**Methods:**

In a single visit, participants visiting Portsmouth Hospital’s asthma clinic with a diagnosis of asthma will be asked to complete a 20-minute questionnaire on an iPad about their psychological and behavioral barriers following the theoretical domains framework and capability, opportunity, and motivation model. Participants’ data are routinely collected, including demographics, asthma characteristics, asthma control, asthma quality of life, and medication regime, which will be recorded on an electronic data capture form.

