Despite the COM-B model being widespread, there is only one generic self-evaluation questionnaire to assess people’s perceptions of capabilities, opportunities, and motivations intended for use in multiple behaviors and a range of diverse populations [13]. Although there was evidence of this questionnaire’s acceptance, validity, and reliability, this questionnaire has not been used with patients in a medical setting. As a result, this study will be able to further demonstrate the questionnaire’s usefulness and reliability.

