## Methods

### Overview

This study will employ a cross-sectional survey design focusing on adherence to asthma treatment. It will be delivered through REDCap, a web-based platform. Participants will be recruited when attending their routine clinical review with the asthma service or while an inpatient at Queen Alexandra Hospital in Portsmouth, United Kingdom. Routinely collected patient data, including demographics, asthma characteristics, asthma control, and medication regime that is already collected as part of their clinical review, will be recorded on an electronic data capture form (e-CRF) through the REDCap platform. They will then be asked to complete the series of questionnaires, all completed on the web. Patients will also be provided with a paper copy of each questionnaire. When the questionnaire is completed, the user will be provided with debriefing information.

Participants will be asked to complete a set of questionnaires that will assess the following:

Psychological and behavioral barriers that may affect the participant being able to take their asthma treatments as recommended: the brief COM-B questionnaire (which is being validated as part of this study) and the 61-item Theoretical Domain Framework Questionnaire.Their asthma symptoms and how well controlled their asthma is (Asthma Control Questionnaire [ACQ-6]), the impact their asthma has on their quality of life (Mini Asthma Quality of Life Questionnaire), and the level of anxiety or depression they may be experiencing (Hospital Anxiety and Depression Scale). All of these questionnaires are used routinely at clinic reviews.Their use of technology at home and any challenges they face with this: Digital Readiness Questionnaire.

The COVID-19 pandemic has changed the way people with asthma access their care with a move to remote consultations and questionnaire completion. The COM-B questionnaire may well be suitable for this approach. However, it is essential to assess digital readiness in this population to understand whether this is feasible and inform the design of future studies if the COM-B questionnaire proves to be successful.

It should not take more than 20 minutes to complete. The questionnaires are all validated and approval has been granted for their use in this study.

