#### Questionnaires Collected

The asthma COM-B questionnaire [13] measure will be responsible for identifying one’s capabilities, opportunities, and motivations regarding asthma medication adherence. In the questionnaire, these measures will be presented as individual questions, forming 6 matrix tables.

This questionnaire will be brief, with 6 items asking them to rate their understanding of their psychological and physical capacities, opportunities, and motivations for adhering to asthma treatment on a Likert scale (see Figure 3, for example items from the questionnaire adapted from Keyworth et al’s [17] COM-B measure). This tool would follow the structure, formatting, and length of other questionnaires given to patients during their initial assessments. As a result, it will be easily integrated into the health care system, providing health care providers with immediate responses to patients’ psychological needs and potentially getting a better understanding when meeting with the patient.

The ACQ [15,18] consists of 6 items covering day and nighttime symptoms, activity limitations, and rescue bronchodilator use. A score of ≥1.5 reflects poor asthma control.

The Mini Asthma Quality Of Life Questionnaire standardized version [16,19] measures four domains: symptoms, activity limitation, emotional function, and environmental stimuli.

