##### Primary Analysis

The primary analysis will comprise the correlation of outcomes from the brief COM-B questionnaire and the TDF questionnaire, as well as the Spearman rank correlation coefficients (ρ; strength of the relationship) and a hierarchical multiple regression analysis. For example, the capability result of the questionnaire will be compared to knowledge, skills, memory attention and decision processes, behavioral regulation, and skills. In addition, some exploratory analysis between the variables will be conducted—this will be used to derive the content validity of the brief COM-B questionnaire.

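### The planned COM-B/TDF associations support convergent, not content, validity, and one visit with apparently one item per component cannot show test-retest or per-component reliability

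*Protocol article*

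**What the plan says.** Under Statistical Analysis, Primary Analysis, the protocol article states: "The primary analysis will comprise the correlation of outcomes from the brief COM-B questionnaire and the TDF questionnaire". Spearman coefficients and a hierarchical multiple regression are named alongside, with one example that sets the capability result against its TDF domains. The section then adds unspecified exploratory analysis between variables and says "this will be used to derive the content validity of the brief COM-B questionnaire".

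In the Introduction, under The Theory, the article notes that the generic questionnaire has not been used with patients in a medical setting, and concludes that "this study will be able to further demonstrate the questionnaire’s usefulness and reliability".

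The design is fixed elsewhere. The Abstract's Methods begin "In a single visit", and the Methods Overview says "This study will employ a cross-sectional survey design focusing on adherence to asthma treatment". Under Questionnaires Collected: "This questionnaire will be brief, with 6 items". Sampling and Sample Size counts six COM-B components. The Methods Overview also says that the brief questionnaire is being validated in this study.

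**The concern.** The article attaches two measurement properties to a design that does not deliver them as stated. The first is a wrong label: the analysis is associational, while content validity is established by judging the items. The second is a promise without a design behind it: reliability needs either a repeat administration or several items measuring the same thing.

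This matters because validation is a stated purpose and the tool is meant for use with individual patients in clinic. For that use, the reliability of each single-item score is the property a clinician most needs, and this study cannot report it. The label also affects the analysis. Convergent and discriminant validity call for a comparison of matched with unmatched pairs, whereas the content-validity label points to no particular comparison.

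**Working it through.** The plan gives no figure for either property, so there is nothing to reproduce. Its sample-size figure for a correlation does not bear on this point.

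**1. Is there a route to content validity?** The analysis headings (Overview, Summary Statistics, Primary, Secondary and Exploratory Analysis, missing data) name correlations, regressions, t tests, ANOVA, cluster analysis and network analysis. All of these work on scores. None is a rating of item relevance or completeness by experts or patients, or a cognitive interview. The Patient Public Involvement Process section covers research questions, objectives, recruitment and clinic logistics, the information sheet and the lay summary. It does not mention review of the COM-B items.

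**2. Is there a route to reliability?**
- Administrations per participant: 1 (Abstract, Methods; Methods Overview). Test-retest needs at least 2, so no repeat pair exists.
- Items per component: 6 items / 6 components = 1. Internal consistency needs at least 2 items per score, so it is undefined for each component.
- Reliability coefficients estimable for the six component scores: 0.
- Reliability statistics named in the analysis sections: none.

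**3. What could be computed from one visit?** Pooling is possible. With average inter-item correlation r, a two-item score (for example, psychological with physical capability) has coefficient 2r/(1 + r), and a six-item total has 6r/(1 + 5r). The values of r below are assumptions.

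| r | two items | six items |
|---|---|---|
| .2 | .33 | .60 |
| .3 | .46 | .72 |
| .5 | .67 | .86 |

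These describe pooled scores, not the six component scores that the analysis Overview plans to tabulate.

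**4. Does the TDF correlation identify reliability indirectly?** Under classical test theory with uncorrelated errors, observed r = true correlation × √(COM-B reliability × TDF reliability). Take an observed r of .50 and a TDF reliability of .85, both assumed.

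| COM-B item reliability | true correlation implied |
|---|---|
| .40 | .50/√(.40 × .85) = .86 |
| .60 | .50/√(.60 × .85) = .70 |
| .80 | .50/√(.80 × .85) = .61 |
| .95 | .50/√(.95 × .85) = .56 |

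One observed correlation fits all four rows. It gives only a lower bound, reached when the true correlation is 1: .50²/.85 = .29.

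**5. What can the data support?** Table 1 defines the matched pairs. Counting its entries as printed:

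| Component | matched domains | unmatched (of 14) |
|---|---|---|
| Psychological capability | 4 | 10 |
| Physical capability | 1 | 13 |
| Social opportunity | 1 | 13 |
| Physical opportunity | 1 | 13 |
| Reflective motivation | 6 | 8 |
| Automatic motivation | 4 | 10 |
| Total | 17 | 67 |

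The total is 6 × 14 = 84 cells. The 17 entries cover 14 distinct domains, because skills, role and identity, and optimism each appear twice. Provided that the 61-item questionnaire yields a score for each domain, this matrix comes from data already being collected.

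**The case against.** The strongest reply is that this is a matter of labels. The Introduction's Overview describes the aim correctly, as checking whether the brief tool finds the same barriers as longer questionnaires, which is a convergent aim. Content validity is named once and reliability is claimed for this study once. A reader might infer that the study's headline conclusions would assert both properties. The documents do not support that: neither the Abstract's Conclusions nor the Discussion mentions either one, and no reliability result is promised in the analysis sections.

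A reader might also infer that a single visit carries no information on reliability at all. That is too strong. The article sometimes works with capability, opportunity and motivation as three constructs, and a two-item coefficient for each, or an alpha over all six items, could be computed. None is planned, and each would pool components that the model treats as distinct.

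Two further points deserve weight. Grammatically, the content-validity sentence refers to the added exploratory analysis, not to the main correlations, and its detail may sit in a fuller document. It is still described as analysis between variables, so the label remains wrong. Also, Questionnaires Collected mentions six matrix tables, which might hold several rows, and the layout figure is not shown. The six-item count and the Figure 3 caption favour one item per component but do not prove it.

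Finally, the article cites earlier evidence of reliability for the generic questionnaire. That is background. It does not show that this study, with an adapted version, will add to it.

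**Conclusion.** The point holds in a limited form. The exploratory between-variable analysis, together with the COM-B/TDF correlations, can support convergent validity and, with unmatched pairs examined, discriminant validity. It does not establish content validity, and no item-content review is described. An unreported review would not change this, because the sentence attributes content validity to analysis of scores.

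The reliability statement is unsupported for test-retest and for each of the six component scores, where the number of estimable coefficients is 0. It is not unsupported in every sense, since pooled coefficients are computable. The per-component part assumes one item per component. The test-retest part rests only on the single visit, to which an analysis plan could not add a repeat administration. The planned correlations themselves remain valid; what changes is the inference attached to them.

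**What to change.** In Primary Analysis, replace content validity with convergent and discriminant validity. State that it will be assessed from the COM-B by TDF-domain Spearman matrix, by checking that the pairs matched in Table 1 correlate more strongly than the unmatched pairs. Say how domains listed under two components are counted.

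In The Theory, delete reliability, or state that test-retest and per-component reliability are not assessed. If a pooled two-item or six-item coefficient is wanted, name it as pooled.

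The cost is two changes of wording and one matrix from data already collected. The downside is a slightly narrower stated scope. Keeping the present claims would instead need an item-content review and a retest sample, which is a larger change to the study.

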##### Exploratory Analysis

Network analysis between variables including (but not limited to):

Type of asthma (T2 or non-T2 defined by the presence of a T2 inflammatory signal assessed using FeNO and peripheral blood eosinophil count)Asthma severity using British Thoracic Society or Scottish Intercollegiate Guidelines Network (SIGN) stageLevel of asthma control assessed using the ACQ6 questionnaire (a score of ≥1.5 reflects poor asthma control)Quality of life measured using the mini-asthma quality-of-life questionnaire scoreNumber of comorbiditiesComplexity of treatment (number of inhaled doses per day, total number of medications taken each day)Informative analysis of digital readiness will be performed by summarizing all participants combined responses, reported in percentages

##### Procedure for Missing, Unused, or Spurious Data

There are no plans for multiple imputations or other corrections for missing data.

### Ethical Considerations

#### Statement of Compliance

All staff working on this study will hold evidence of good clinical practice training before undertaking any responsibilities, and all staff working within the research study team are also part of the respiratory clinical care team and are involved in PhD supervision. Written informed consent will be obtained from all participants after an adequate explanation of the aims, methods, and anticipated benefit of the study using the participant information sheet. A signed copy of the consent form will be given to the participant, and copies will be filed in the study master file and the participants’ medical notes.

Participants’ anonymity will be maintained throughout by identification on a password-protected electronic database and e-CRFs only by initials and participant ID number. All documents will be stored securely and only accessible by study staff and authorized personnel; the study will comply with the Data Protection Act.

#### Potential Benefits or Risks of Study Participation

This study is a low-risk questionnaire study; however, any risks to the participants have been carefully considered—any participants who were observed struggling with the psychological aspect of the questionnaire or the questionnaire raised further issues patients will have these errors highlighted and will be informed with the correct health care professional to look after their care. This is a beneficial outcome for participants’ self-care and management and ensures that they obtain the correct level of care.

This study analyzes a wide variety of behavioral barriers and will help provide a clear picture of the psychological needs that are associated with asthma adherence. Understanding this information is important in the context of managing lung conditions, from treating patients in primary care through to feeding this information back to intervention designers.

#### Other Ethical Considerations

The study will not be initiated before the protocol, and the survey’s material such as the consent forms, survey answers, and participant information sheets have received favorable opinions from the health research authority and the respective NHS research and development (R&D) departments. Should an amendment be made that requires Research Ethics Committee (REC) approval, as defined by REC as a substantial amendment, the changes will not be instituted until the amendment has been reviewed and received approval or favorable opinion from the REC and R&D departments. However, a protocol amendment intended to eliminate an apparent immediate hazard to participants may be implemented immediately, providing that the REC is notified as soon as possible, and approval is requested. Other amendments will be implemented under the direction of the REC.

All participants will have adequate time to consider participation in the study, as per good clinical practice guidelines.

Participants who are already enrolled in other research surveys will be invited and allowed to participate in the study if they so wish.

#### Patient Public Involvement Process

Patients having first-hand knowledge of coping with chronic respiratory disease were sought out for patient involvement in this study. We have spoken with our respiratory patient representatives in person, over the phone, and via email. These individuals have participated in earlier research projects and have lived with respiratory problems. To ensure that we address the issues that are pertinent to persons with airway disorders, they helped define the main questions and establish our study objectives. To reduce waiting times for patients who decided to participate in the study, assistance was also sought with the design of participant recruitment and the implementation of the study within a typical clinical visit. Additionally, they contributed to creating the participation information sheet and cowrote the lay summary.

## Results

The study is already underway, and it is anticipated that the results will be available by early 2023.

## Discussion

The COM-B asthma study will investigate an easily accessible theory-based tool (a questionnaire) for identifying psychological and behavioral barriers in patients with asthma who are not adhering to their treatment. This will provide useful information on the behavioral barriers to asthma adherence and whether or not a questionnaire can be used to identify these needs. The highlighted barriers will increase health care professionals’ knowledge of this important subject, allowing for practice change and better information for interventions to remove those barriers. Overall, this will enable health care professionals to use effective individualized interventions to support improved medication adherence while also recognizing and meeting the psychological needs of patients with asthma.

## Abbreviations

ACQ: asthma control questionnaire
COM-B: capability, opportunity, and motivation model of behavior change
e-CRF: electronic data capture form
FeNO: fractional exhaled nitric oxide
MPR: medicines possession ratio
NHS: National Health Service
R&D: research and development
REC: Research Ethics Committee
SIGN: Scottish Intercollegiate Guidelines Network
T2: type 2
TDF: theoretical domains framework
